### Statistical analysis

Investigators will remain blinded to the penicillin dosage received by each participant until all data are collected. Each binary outcome (presence or absence of Strep A on collected samples) will be assessed against the dose received by participants and whether they were confirmed as meeting the primary study endpoint (diagnosed pharyngitis). Such analysis will allow for an assessment of transmission potential among symptomatic, asymptomatic and non-cases. Frequencies and percentages will be summarized and chi-square statistics will be used for further analyses.

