## Abstract

*

Streptococcus pyogenes

* (also known as group A *

Streptococcus

*, Strep A) is an obligate human pathogen with significant global morbidity and mortality. Transmission is believed to occur primarily between individuals via respiratory droplets, but knowledge about other potential sources of transmission via aerosols or the environment is limited. Such knowledge is required to design optimal interventions to control transmission, particularly in endemic settings. We aim to detail an experimental methodology to assess the transmission potential of Strep A in a clinical environment. We will examine potential sources of transmission in up to 20 participants recruited to the Controlled human infection for penicillin against *
Streptococcus pyogenes* (CHIPS) Trial. Three approaches to understanding transmission will be used: the use of selective agar settle plates to capture possible droplet or airborne spread of Strep A; measurement of the possible distance of Strep A droplet spread during conversation; and environmental swabbing of personal and common high-touch items to detect the presence of Strep A on hard and soft surfaces. All methods are designed to allow for an assessment of transmission potential by symptomatic, asymptomatic and non-cases. Ethical approval has been obtained through Bellberry Human Research Ethics Committee (approval 2021-03-295). Trial registration number: ACTRN12621000751875. Any results elicited from these experiments will be of benefit to the scientific literature in improving our knowledge of opportunities to prevent Strep A transmission as a direct component of the primordial prevention of rheumatic fever. Findings will be reported at local, national and international conferences and in peer-reviewed journals.

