## Method and analysis

### Study design

This sub-study forms a component of the Controlled human infection for penicillin against *
Streptococcus pyogenes* (CHIPS) Trial, (registration number ACTRN12621000751875), a double-blind, placebo-controlled, randomized trial using a previously described human challenge model [31]. Briefly, the CHIPS Trial is designed to determine the optimal dose of penicillin needed to prevent Strep A pharyngitis, conducted in a purpose-built research facility resembling a hospital ward managed by a contract research organization (CRO). All potential participants undertake screening throat swabs and a serum *emm*75 type-specific serology to exclude Strep A carriage or prior infection with the same strain. Each participant is then randomized to receive one of five doses of steady-state penicillin infusions – 0 (placebo), 3, 6, 12 and 20 ng/mL – prior to receiving a direct oropharyngeal challenge with an inoculum of the *emm*75 strain of Strep A via a ‘reverse’ throat swab [32, 33]. Participants are then monitored for development of Strep A pharyngitis according to pre-specified outcome criteria during a confinement period lasting up to 6 days. All participants will be treated as possible infections. This sub-study involves three separate – but related – experiments (detailed below).

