### Study procedures

**1. The capture of environmental Strep A in the vicinity of a potential infection**

Experiments will be completed at three timepoints: 24, 36 and 48 hours following inoculation of the participant with Strep A (the challenge, Day 1). Prior to inoculation, one removable adhesive shelf will be placed on a solid wall 2 metres above the floor in each of the participant’s inpatient cubicles. At 09 : 00 on Day 2 (24 hours post-challenge) one horse blood agar containing colistin and nalidixic acid (HBA-CNA, Pathwest, WA, Australia) selective settle plate will be placed on each shelf and another on the overbed tables of participants. HBA-CNA settle plates that allow Strep A growth and minimize the overgrowth of swarming Gram-negative bacteria will be used throughout [34]. These will remain in position for 4 hours and be removed at 13 : 00. This same process will be repeated on Day 3 (48 hours post-challenge). Settle plates will also be placed in the same positions described above whilst participants are sleeping (approximately 36 hours post-challenge). These will be placed at 22 : 00 on Day 2 (~36 hours post-challenge) and remain in place for 8 hours, before removal at 06 : 00 on Day 3.

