**2. The distance that Strep A droplets move beyond a suspected infection**

These experiments will be completed at two time points: 24 hours post-challenge and 48 hours post-challenge, commencing at 09 : 00 on Days 2 and 3, respectively. Participants will be seated on their beds in front of a table draped with a sterile mat and adjusted to be the same height as their chest. The table will be exactly 30 centimetres (cm) from the chest of the participant and will hold the HBA-CNA settle plate (Fig. 1). To understand transmission during speaking, the participant will be asked to count upwards from one in a conversational tone for one minute as recorded by a stopwatch. At the conclusion of the minute, the participant will cease counting, and the plate will remain in place for an additional minute to capture any droplets that may still be falling. The experiment will be repeated in the manner described above with new plates placed at distances of 90 and 180cm [14, 28].

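### The pharyngitis endpoint has two levels, so the named analysis cannot deliver the promised comparison of symptomatic, asymptomatic and non-cases, and that status may be fixed after the samples were taken

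*Protocol article*

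**What the plan says.** The Statistical analysis section names two explanatory variables. Each binary sample result "will be assessed against the dose received by participants and whether they were confirmed as meeting the primary study endpoint (diagnosed pharyngitis"). The next sentence draws the conclusion: "Such analysis will allow for an assessment of transmission potential among symptomatic, asymptomatic and non-cases". Frequencies and percentages follow, with chi-square statistics. The Abstract makes the claim for the whole sub-study: "All methods are designed to allow for an assessment of transmission potential by symptomatic, asymptomatic and non-cases". The article defines none of the three labels.

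On timing, Study design describes how the endpoint is ascertained: "Participants are then monitored for development of Strep A pharyngitis according to pre-specified outcome criteria during a confinement period lasting up to 6 days". Sampling is much earlier. For the settle plates: "Experiments will be completed at three timepoints: 24, 36 and 48 hours following inoculation of the participant with Strep A (the challenge, Day 1". The droplet experiment runs at "24 hours post-challenge and 48 hours post-challenge, commencing at 09 : 00 on Days 2 and 3, respectively", and the environmental swabs follow it.

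The Discussion mentions symptom assessment around the sampling periods, and nasal and throat samples. It gives these data an analytic use only for recognising contamination between participants.

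**The concern.** Three clinical groups are promised, but the only clinical variable named has two values. The analysis as described would produce a symptomatic versus everyone-else table. A reader of the eventual report could take the second row as showing how much asymptomatic carriers shed, when it mixes carriers with people who were never infected. Deciding the groups after the data are seen would also leave room for choice in a sample of at most 20.

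The second issue is what the label means at the time of sampling. If endpoint status is fixed by the end of confinement and applied to all of a participant's samples, someone diagnosed after Day 3 is counted as symptomatic for samples taken while still without symptoms. That would dilute the contrast between cases and others.

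A related matter is that dose may influence both diagnosis and shedding. The Discussion itself says that penicillin may make recovery of Strep A from plates and swabs less likely. An unstratified comparison by diagnosis could then partly reflect dose.

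**Working it through.** The article states no power, effect size or significance level, and no formal sample size calculation was done, so there is no figure to reproduce.

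**1. Levels against groups.** The endpoint has 2 levels and 3 groups are promised. Crossing it with the 5 doses gives 5 × 2 = 10 cells, but dose is assigned treatment, not infection status. Within any dose, asymptomatic infection and no infection share the cell for endpoint not met.

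Let *w* be the share of that cell that is infected, and *pA* and *pN* the positivity in asymptomatic and uninfected participants. Only the mixture *w·pA* + (1 − *w*)·*pN* is observed: one equation in three unknowns. Even with *w* = 0.5 known, a mixture positivity of 10% fits any *pA* from 0 to 20% (if *pN* = 0, *pA* = 0.10/0.5 = 20%). Both 10% and the equal split are assumed.

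**2. Timing.** Taking 09:00 on Day 2 as 24 h, 09:00 on Day 3 is 48 h. The last timed plate comes off at 13:00 on Day 3, which is 48 + 4 = 52 h. With challenge on Day 1, a diagnosis on Day 6 would come 6 − 2 = 4 days after the Day 2 samples and 6 − 3 = 3 days after the Day 3 samples. If the window were 6 × 24 h from challenge, the lags would be 5 and 4 days. If confinement starts before challenge, they are shorter. These are upper bounds, because the article gives no diagnosis times.

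**3. What such a lag could cost.** Assumptions, none from the documents: 10 eventual cases and 10 others; positivity 60% in those symptomatic at sampling and 10% in everyone else; a fraction *f* of eventual cases not yet symptomatic. Positivity among eventual cases is 0.6(1 − *f*) + 0.1*f*, so the difference from the others is 0.5(1 − *f*).

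| *f* | Positivity, eventual cases | Difference (points) | Approximate power |
|---|---|---|---|
| 0 | 60% | 50 | 67% |
| 25% | 47.5% | 37.5 | 45% |
| 50% | 35% | 25 | 26% |
| 75% | 22.5% | 12.5 | 11% |

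**4. Dose as a common cause.** Suppose diagnosis has no effect on shedding within a dose, with 4 participants per dose. If *d* is the probability of diagnosis and *s* that of shedding at each dose, expected positivity is Σ*ds*/Σ*d* in the diagnosed and Σ(1 − *d*)*s*/Σ(1 − *d*) in the rest. All rates, listed from placebo to the highest dose, are assumed. The last column is the simulated rejection rate of Fisher's test at 5%.

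| Diagnosis and shedding by dose (%) | Diagnosed | Not diagnosed | Rejects |
|---|---|---|---|
| 80/65/50/25/10 for both | 1.385/2.30 = 60% | 0.915/2.70 = 34% | about 12% |
| 70/60/50/35/20 for both | 1.2625/2.35 = 54% | 1.0875/2.65 = 41% | about 4% |
| 60/55/50/40/30 for both | 1.1625/2.35 = 49% | 1.1875/2.65 = 45% | about 2% |
| Diagnosis as in row 1; shedding 30/25/20/10/5 | 0.5325/2.30 = 23% | 0.3675/2.70 = 14% | about 3 to 4% |

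With no dose effect, the test rejects about 2% of the time. Only the steepest gradient moves it materially.

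**5. Group sizes after a fix.** With 20 participants, assumed splits of 50/25/25%, 30/30/40% and 60/20/20% give 10/5/5, 6/6/8 and 12/4/4. For a group of 5 with no positives, the exact 95% upper limit is 1 − 0.025^(1/5) = 52%; for 4 it is 1 − 0.025^(1/4) = 60%.

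**The case against.** The strongest reply is that an article condenses the full protocol. The sub-study is part of the CHIPS Trial protocol, which has its own outcome criteria and evidently takes nasal and throat samples, so definitions of the three groups may exist there. That answers any complaint about missing definitions. It does not answer the sentence itself, which says that the analysis just described, by dose and endpoint status, yields the three-group assessment. It does not.

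Three stronger readings are tempting, and the documents support none of them.

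- A reader might infer that the case comparison is in fact blurred by late diagnoses. The article gives only the maximum length of confinement. It also says that sampling coincides with symptom assessment, so same-day symptom data are described. Misclassification is possible, not shown.
- A reader might infer that the plan contradicts its Discussion, which says that penicillin concentration has to be taken into account. There the subject is whether standard infection control suffices without physical isolation. It is not a commitment to adjust the comparison by diagnosis. Dose is also a named analysis factor; whether it is used jointly with diagnosis is left open.
- A reader might treat shedding by asymptomatic carriers as the study's main contrast. The Study objectives section does not list it.

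It is also fair to say that this is a descriptive pilot, that the flaw can be mended without changing sample collection, and that within-dose testing at about 4 per dose has little power. All three points stand, and they limit the severity and shape the remedy.

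**Conclusion.** The mismatch between two levels and three groups holds with no assumption beyond the article's own wording: asymptomatic infection cannot be separated from no infection with the variables named. The timing point holds as a possibility, bounded by samples ending at about 52 h and monitoring of up to 6 days. Its effect under the assumed rates runs from no loss to a fall from 50 to 12.5 points. Dose may distort the comparison by diagnosis, but the size depends entirely on assumed gradients, with rejection from about 2% to 12%, and it is a supporting remark only. The point should be fixed before analysis. It is not critical, because the sub-study is a pilot of up to 20 reported mainly as frequencies.

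**What to change.** - Define three groups in the analysis section from parent-trial data: throat or nasal culture positive with pharyngitis; culture positive without pharyngitis; culture negative.
- Classify each sample by the culture and symptom status nearest its collection time, where the parent trial's schedule allows. The article gives no culture schedule, and the overnight plate may have no matching culture, so state the rule for the nearest result.
- Keep final endpoint status as a separate, labelled comparison.
- Report counts and percentages with exact intervals, and tabulate the comparison by diagnosis within dose, descriptively and without a within-dose test.
- If the linkage is not feasible, remove the three-group claim from the Abstract and the Statistical analysis section and describe the comparison as endpoint met versus not met.

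The cost is revised wording and linkage to the parent trial's cultures and symptom records; the article suggests that no new sampling is needed. The downside is small groups, perhaps 4 to 6 in the smallest, with wide intervals that will not support firm conclusions about asymptomatic shedding.

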### Sample size

The CHIPS Trial will be recruiting 60 participants as dictated by sample size calculations [31]. For this pilot sub-study, a formal sample size calculation has not been performed. Instead, a pragmatic approach dictated by resource and personnel constraints has been adopted and up to 20 participants will be enrolled. All participants will consent to participate in the sub-study at the time of trial enrolment and will provide verbal consent to participation at the first time point (24 h post-challenge).

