**3. The environmental assessment of the confinement room via swabbing**

Following the completion of the droplet transmission experiments, environmental swabs of five items belonging to each participant will be collected. These will include one personal item as determined by the participant, the bed remote control, bedside table, water bottle/cup and intravenous (IV) stand. Flocked swabs (Conan regular flocked swab breakpoint in peel pouch sachet; Copan, Italy) selected for appropriateness of use and transport with our selected medium will be moistened with two to three drops of sterile saline and rolled over the selected object/surface in at least two different diagonal directions across a surface area of approximately 25 cm^2^. Swabs will be placed immediately in a cryovial containing 0.5 ml of skim milk, glucose, glycerol broth (SGGB) solution (PathWest Media) kept at 4–8 °C. In addition, 10 common, high-touch areas in the confinement room will be swabbed using the same methodology, selected based on observation of the room during morning vital checks. A timeline demonstrating when each experiment will occur can be seen in Fig. 2.

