### Microbiological analysis

All swabs and CNA plates collected will undergo transfer and processing for microbial culture for beta-haemolytic streptococci (BHS) using gold standard culture methodology [35] and according to Clinical and Laboratory Standards Institute (CLSI) standards. If no bacterial growth is observed after 24 hours, incubation will be extended for a further 24 hours to allow growth of slow-growing or small colonies. The presence of Strep A as indicated by β-haemolytic morphology will be confirmed with subculture, bacitracin sensitivity testing and positive group A latex agglutination reaction (Streptex, Thermo Scientific). Strep A isolates will be stored at −80 °C to permit further strain characterization. Results will be reported as the presence or absence of Strep A on each sample. Quantitation of the amount of Strep A is not possible with this experimental design.

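### Chi-square tests are named for sample-level outcomes without fixing the unit of analysis, and they fit badly whether samples are pooled or tested one by one

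*Protocol article*

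**What the plan says.** The outcome is defined on samples and the comparison factors on people. Under Statistical analysis: "Each binary outcome (presence or absence of Strep A on collected samples) will be assessed against the dose received by participants", and also against whether the participant met the pharyngitis endpoint. The only inferential method follows: "Frequencies and percentages will be summarized and chi-square statistics will be used for further analyses". Under Microbiological analysis: "Results will be reported as the presence or absence of Strep A on each sample".

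The number of people is small. Under Sample size, "up to 20 participants will be enrolled". Under Study design, "Each participant is then randomized to receive one of five doses of steady-state penicillin infusions".

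Each person is sampled many times. For experiment 1, "Experiments will be completed at three timepoints: 24, 36 and 48 hours following inoculation", and at each time one "selective settle plate will be placed on each shelf and another on the overbed tables of participants". Experiment 2 uses three distances on two days. Experiment 3 swabs five items per participant, and in addition "10 common, high-touch areas in the confinement room will be swabbed using the same methodology".

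The article does not say whether a table counts samples or people, and it gives no per-participant summary and no allowance for repeated samples. It does not say how the common-area swabs relate to the comparisons by dose and diagnosis.

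**The concern.** Dose and diagnosis vary only between participants. Someone who sheds heavily can be expected to contaminate several of their own plates and items, so samples from one person are unlikely to be independent. The ordinary chi-square test assumes independent observations. If samples are stacked in one table, one or two heavy shedders could produce an apparent dose or disease effect.

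If each sample type and time has its own table, independence within a person is no longer an issue. The tables then become too sparse for a large-sample test, and there are many of them.

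The common-area swabs raise a smaller, separate point. They come from space that participants share, so they carry no participant and no dose. The phrase about collected samples does not exclude them from the comparison with dose.

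What is at stake is how far the sub-study's statements about penicillin dose and transmission potential, which Study objectives anticipates, can rest on its p-values.

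**Working it through.** The article gives no power, alpha or sample size figure for the sub-study, so there is none to reproduce.

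**Samples per participant**
- Experiment 1: 2 positions × 3 times = 6 plates.
- Experiment 2: 3 distances × 2 times = 6 plates.
- Experiment 3: 5 item swabs if done once, or 5 × 2 = 10 if done after both droplet sessions. The text can be read either way and the timeline figure is not shown.
- Total: 6 + 6 + 5 = 17, or 6 + 6 + 10 = 22. For 20 participants that is 340 or 440 samples.

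**Assumptions, none given in the article:** nominal level 5%; positivity 10% or 20%; within-participant intraclass correlation (ICC) as shown; 4 participants per dose; 10 with and 10 without pharyngitis.

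**Reading A: samples pooled.** With m samples per person, the design effect is 1 + (m − 1) × ICC. For m = 6 this is 1 + 5 × 0.1 = 1.5 at ICC 0.1 and 1 + 5 × 0.3 = 2.5 at ICC 0.3. Type I error under no effect comes from 40,000 beta-binomial simulations per setting; ranges span the two positivity rates.

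| Samples pooled per person | ICC | Design effect | Diagnosis (10 v 10) | Five doses (4 each) |
|---|---|---|---|---|
| 6 | 0 | 1.0 | 5% | 4–5% |
| 6 | 0.1 | 1.5 | 11% | 15–17% |
| 6 | 0.2 | 2.0 | 17% | 28–32% |
| 6 | 0.3 | 2.5 | 22% | 40–45% |
| 22 | 0.05 | 2.05 | 17% | 32–33% |
| 22 | 0.1 | 3.1 | 27% | 54–55% |

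As an analytic check, the true size is approximately P(χ² > critical value ÷ design effect). For five doses (4 df, critical value 9.488) at design effect 2.5, 9.488 ÷ 2.5 = 3.795. With 4 df the tail probability is exp(−x/2) × (1 + x/2) = exp(−1.898) × 2.898 ≈ 0.43, which agrees with the simulation.

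**Reading B: one table per sample type and time.** Each participant appears once per table.
- Number of tests: 22 sample types and times × 2 factors = 44, or 17 × 2 = 34.
- Row size for dose: 20 ÷ 5 = 4 if balanced. The two expected counts in a row sum to 4, so none can reach 5.
- Expected positives per dose: 4 × 0.1 = 0.4 and 4 × 0.2 = 0.8. Even at 50% positivity it is 2.0.
- Simulated size of the nominal 5% test: five doses, 1.2% at 10% positivity and 3.3% at 20%; diagnosis, 1.0% and 3.0%.

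**The case against.** The strongest reply is that pooling is nowhere stated. The reference to each binary outcome fits one table per position, distance, item and time, and reporting per sample describes the laboratory result, not the unit of analysis. This stands. A reader might infer that the plan treats up to 22 samples per person as independent and that its p-values will be far too small. The text does not support that as fact. On the separate-table reading the individual tests err the other way. They are more conservative still if positivity is lower than assumed, which is plausible for the speech plates because the Discussion cites earlier work that found very limited spread while talking.

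A reader might also infer that the common-area swabs will be attached to individual participants. No section says so, and the planned frequencies and percentages suit those swabs. What remains is that the wording does not exclude them.

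It can further be said that a condensed article may leave the unit of analysis, clustering and multiplicity to fuller documents that are not shown. Silence on those matters would be no finding by itself. But the article does fix a test, and that test fits badly on both readings.

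Finally, this is a pilot without a formal sample size, the dose comparison is only something it may allow, and tests follow descriptive summaries. That lowers the severity but does not make the named test suitable.

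**Conclusion.** The concern holds conditionally. The chi-square test is named for a sample-level outcome against participant-level factors, with no unit of analysis, for at most 20 people who supply 17 samples each (22 on the two-session reading).

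If samples are pooled within one six-plate experiment, type I error is about 11–22% for diagnosis and 15–45% for dose at ICC 0.1–0.3. Pooling all samples is worse. If each sample type and time is tested alone, there is no within-person inflation. The dose tables then have no expected count of 5, size is about 1–3% at 10–20% positivity, and there are up to about 44 tests.

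The sizes rest on the assumed ICC, positivity and group splits. The direction on each reading does not depend on their exact values, provided that samples from one person are positively correlated and positivity is low. Dependence between people through the shared ward is possible on either reading and is not quantified here. This should be fixed; it is not a reason to doubt the pilot's descriptive results.

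**What to change.** Replace the chi-square sentence with text that does the following:
- Makes the participant the unit, with one summary per experiment: any positive sample, or the number positive.
- Uses Fisher's exact or a permutation test for diagnosis, and an exact or permutation test for dose.
- For comparisons by time, distance or item, permutes dose or diagnosis labels between whole participants, or uses a participant-clustered model with a small-sample correction.
- States that the 10 common-area swabs are described only and take no part in the dose and diagnosis comparisons.

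The cost is a few sentences and no new data. One summary for each of 3 experiments against 2 factors gives 3 × 2 = 6 main tests in place of 34 or 44. Compared with a pooled analysis, p-values and intervals become less favourable. Exact tests on 20 people will also have little power, so the descriptive results will still carry most of the weight. An any-positive summary discards detail; the number positive keeps more of it.
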